### Sample size calculations

We expected a change in the primary outcome measure of the incidence of dementia diagnoses and cognitive assessments from 50% to 65% of the total population of dementia. In previous studies on implementation of several other guidelines in general practice the average change was 10% [43]. However, these implementation studies focused on diseases, to which GPs already showed a high adherence to the guidelines. Because of the low adherence to dementia guidelines we saw more room for improvement and therefore we expected a change of 15% to be realistic. Cluster randomisation was taken into account when we calculated the sample size needed. In this calculation, the ratio between the number of duos in the control group and the number of duos in the intervention group was 1:2. Clusters are expected to include 5 patients on average. Intra class correlation (ICC) is expected to be 0.05 or lower. For a power of 0.80, and two-sided testing at 0.05, a total of 91 general practitioners is required.

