## Background

### Diagnosing dementia in primary care

Dementia is an increasing challenge for health care and social systems in developed countries. In Europe, 6.4% of the elderly over 65 years suffer from dementia, with an increase from 0.8% in the group aged 65–69 years to 28.5% at age 90 years and older. The total number of dementia patients in Europe is expected to increase from 7 million in 2000 to over 16 million in 2050 [1]. Currently, dementia seems to be under-diagnosed [2-4]. More than 50% of dementia patients living in the community have not been diagnosed by a GP or specialist [5,6]. In the Netherlands, detection of dementia takes place around one year before admission to a nursing home and three years before death [7], which is rather late.

Early diagnostic evaluation of patients possibly suffering from dementia is beneficial for both patient and caregiver. Reversible causes of dementia will be identified and treated timely. Formal disclosure of dementia diagnosis allows patients and carers to make future plans and provides early access to support services [8]. These actions may prevent or decrease psychological distress in patients [9]. Early education and support for caregivers facilitates adjustment over a longer period of time; it prevents crisis situations and delays nursing home admissions [10,11]. Non-pharmacological interventions, such as psychosocial interventions (10;11) and occupational therapy [12], have been shown to play a key role in dementia management. Pharmacological treatment may primarily be beneficial when started in the early stages of dementia. However, drugs that are currently available have only moderate effect on cognitive symptoms and ADL [13]. In the near future, disease-modifying drugs might become available since they are already subject to phase two and three trials.

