### Outcome measures and data collection

Primary outcome measures are the numbers of cognitive assessments and dementia diagnoses over a period of nine months, which will be measured at baseline (T0) and nine months later, at the end of the study (T1). Secondary outcomes are GPs' and nurses' attitude, confidence and knowledge regarding dementia diagnosis and management, which will be measured at baseline (T0) and nine months later, at the end of the study (T1). Other secondary outcomes are the rate of adherence to national guidelines for dementia diagnosis and management, patient satisfaction, informal carer burden and satisfaction, number of emergency calls, visits and consultations. Baseline demographic characteristics collected from GPs and nurses are: age, sex, practice experience, practice size, percentage of elderly people > 65 years and the availability of chronic disease management programs in practice. Baseline demographic characteristics collected from patients and their informal caregivers are: age, sex and co-morbidity (Table 1).

**Table 1 T1:** Outcome measures

**Variable**	**Primary outcomes**	**Secondary outcomes**	**Background**	**Instrument/Source**	**T_0_**	**T_1_**	**T_x_**

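### The stated 80% power is for a proportion of all people with dementia, not for the nine-month counts that are the primary outcomes

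*Protocol article*

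**What the plan says.** The Sample size calculations section of the protocol article bases the target effect on the "incidence of dementia diagnoses and cognitive assessments from 50% to 65% of the total population of dementia". Its other inputs are:

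- Allocation: "the ratio between the number of duos in the control group and the number of duos in the intervention group was 1:2".
- Cluster size: "Clusters are expected to include 5 patients on average".
- Clustering: "Intra class correlation (ICC) is expected to be 0.05 or lower".

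It concludes: "For a power of 0.80, and two-sided testing at 0.05, a total of 91 general practitioners is required". The Study population section plans 100 duos.

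The Outcome measures and data collection section defines the endpoint differently: "Primary outcome measures are the numbers of cognitive assessments and dementia diagnoses over a period of nine months". The Abstract and a footnote to Table 1 agree that these are numbers over nine months. They are measured at baseline (T0) and again at nine months (T1). The sources are the GPs' electronic records, interviews and self-registration forms. The Statistical analysis section names MANOVA as the confirmatory method.

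**The concern.** The article gives two descriptions of the primary outcome, and they conflict. The power statement treats it as a patient-level proportion whose denominator is everyone with dementia. The outcome section treats it as a count with no denominator.

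The proportion cannot be formed from the planned data. No row of Table 1 and no listed source gives the number of people with dementia per practice. Practice size and percentage of elderly patients are collected, but only as background. The Background section itself says "More than 50% of dementia patients living in the community have not been diagnosed by a GP or specialist", so records cannot supply the denominator.

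For cognitive assessments the proportion does not fit even in principle. The Study population section targets frail elderly people suspected of cognitive problems, and some of those assessed will not have dementia.

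At stake is how the result is read. A null finding on the counts would be judged against an 80% power claim that belongs to a different test.

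**Working it through.** **1. Reproduce the stated figure.** Inputs, all from Sample size calculations: p₁ = 0.50, p₂ = 0.65, ratio 1:2, two-sided alpha 0.05, power 0.80, 5 patients per cluster, ICC 0.05.

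- Pooled proportion: (0.50 + 2 × 0.65)/3 = 0.60.
- Control n = [1.96·√(0.60 × 0.40 × 1.5) + 0.842·√(0.25 + 0.2275/2)]² / 0.15² = 126. Intervention n = 252. Total 378.
- Design effect: 1 + (5 − 1) × 0.05 = 1.20.
- GPs: 378 × 1.20 / 5 = 90.7, so 91. The unpooled variance gives 91.4.

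The arithmetic is correct, and the 80% belongs to this two-proportion test.

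**2. Move to the count.** The article gives no mean count, standard deviation or count distribution, so each row below rests on an added assumption. Take one GP per duo, so 91 gives 30.3 v 60.7 and 100 gives 33.3 v 66.7.

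- Difference scale: power = Φ(d / SE − 1.96), with SE = √(V₁/n₁ + V₂/n₂).
- Log rate-ratio scale: power = Φ(ln 1.3 / SE − 1.96), with SE = √{φ[1/(m₁n₁) + 1/(m₂n₂)]}, where φ is variance divided by mean.

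*Reading A: 5 is the mean number of dementia patients per duo.* The means are 5 × 0.50 = 2.5 and 5 × 0.65 = 3.25, so d = 0.75.

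Example with Poisson variance and 91 duos: SE = √(2.5/30.33 + 3.25/60.67) = 0.369. Power = Φ(0.75/0.369 − 1.96) = 0.53.

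The stated ICC can be kept. If the number of patients N per duo is Poisson with mean 5, then E[N(N − 1)] = 25 and V = p(1 − p)(5 + 25 × 0.05) + 5p². This gives V₁ = 2.81 and V₂ = 3.53. At 91 duos SE = 0.389 and power is 0.49.

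If instead every duo has exactly 5 patients, V = 5p(1 − p) × 1.2, so V₁ = 1.50 and V₂ = 1.365. SE = 0.268 and power is 0.80, as stated.

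*Adjustment for the T0 count.* Multiply SE by √(1 − r²), where r is an assumed correlation between baseline and follow-up counts.

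*Reading B: 5 is the control-arm count.* The means are 5 and 5 × 1.3 = 6.5.

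| Assumption | 91 duos: difference / log | 100 duos: difference / log |
|---|---|---|
| A, variance = mean | 0.53 / 0.49 | 0.57 / 0.53 |
| A, variance = 2 × mean | 0.30 / 0.28 | 0.33 / 0.30 |
| A, Poisson N, ICC 0.05 | 0.49 / – | 0.53 / – |
| A, variance = mean, r = 0.5 | 0.65 / 0.61 | 0.69 / 0.65 |
| A, variance = mean, r = 0.7 | 0.81 / 0.78 | 0.85 / 0.81 |
| B, variance = mean | 0.82 / 0.78 | 0.85 / 0.82 |
| B, variance = 2 × mean | 0.53 / 0.49 | 0.57 / 0.53 |

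All rows concern a single count. The planned MANOVA would test the two counts jointly, and the article gives no correlation between them.

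**The case against.** The strongest reply is that no shortfall has been shown. The section says only that clusters hold 5 patients on average, without saying whether these are all dementia patients at risk or patients assessed. The Case-based coaching program section has duos selecting patients over nine months, which makes the second reading possible. Under it, Poisson power is close to 80%. Baseline counts are also measured, and using them could recover much of any loss. This stands: the documents do not fix the size of the loss, or that there is one.

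A reader might infer that the plan's own inputs give about 53% power. They do not. That figure adds Poisson variance and Reading A, neither of which the article states. It also drops the stated ICC, uses 91 rather than the planned 100 duos, and ignores T0 adjustment.

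A reader might also infer that the 50% is the share of existing cases already diagnosed. The section calls it incidence and does not tie it to the Background figure, so this cannot be established.

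Finally, a separate analysis plan may specify the count model. The absence of a mean count from an article is therefore not itself the fault. The fault is that the article attaches its power to a quantity other than its primary outcome, and that conflict is in its own text.

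**Conclusion.** The point holds as a mismatch between endpoint and sample size. The arithmetic is right for the proportion. The 80% is not the power of a test on the nine-month counts, and the article contains nothing from which that power could be fixed.

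Conditional values are:

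- **Reading A, unadjusted:** about 0.28 to 0.57 (variance one to two times the mean, 91 to 100 duos). With Poisson cluster size and the stated ICC it is 0.49 at 91 and 0.53 at 100. It reaches 0.80 at 91 only if every duo has exactly 5 dementia patients, although the article gives 5 as an average.
- **Reading A, T0-adjusted, Poisson variance:** about 0.61 to 0.69 at an assumed correlation of 0.5, and 0.78 to 0.85 at 0.7.
- **Reading B, Poisson variance:** about 0.78 to 0.85, and lower with overdispersion.

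The supportable statement is that power for the primary outcomes is not established. A flat claim that the trial is underpowered goes further than the documents allow.

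**What to change.** In Sample size calculations, replace the 50% to 65% target with an effect on the nine-month count per duo, stated for each primary outcome. Give:

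- the expected control mean and the between-duo variance, both taken from T0 data, which are collected before randomisation;
- a target rate ratio;
- an allowance for clustering by the randomised unit, which under Bias control and randomisation can hold more than one GP.

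Adjust the primary analysis for the T0 count. Report the power that the planned 91 to 100 duos give on that scale in place of 0.80, with a range if the baseline correlation is still uncertain.

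The cost is some rewording and one recalculation. No extra duos are needed to state the power correctly. The downside is that the stated power may become less favourable.

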### Bias control and randomisation

Randomisation will take place after measurement of baseline data. Duos of GPs and nurses will be randomly allocated to one of the two conditions: 1. Dementia Training Program (DTP) and 2. no training at all; control group. (Figure 1). Randomization will be concealed; a person who is not responsible for recruiting subjects and has no knowledge of the study conduct will perform it on a computer.

Cluster-randomisation will be performed in order to avoid contamination by the effects of possible exchange of information within a cluster. A cluster was defined as all GPs working in the same practice or as all GPs working together with the same nurse.

In order to assure an equal distribution of baseline characteristics, duos will be randomised with adaptive weights regarding cluster size (one vs. more than one GP), age, sex, high or low percentage of elderly patients in practice (< or > 15%), practice location (rural or urban area) and nurse affiliation (district or practice).

Adherence to guidelines will be assessed by two independent researchers. In order to exclude the possibility of detection bias, these researchers will be blinded to the outcome of randomization.

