Secondly, we cannot exclude the possibility of contamination arising by chance contacts and possible knowledge exchange between GPs and nurses from different allocation conditions. We try to overcome this problem by cluster randomization: GPs from the same practices and GPs working with the same nurses are allocated to the same group.

Finally, performance bias can occur. GPs and nurses are fully aware of their assignment to either the experimental or the control group. We try to overcome this problem by reminding participants in the control group every two months of their involvement in the study.

In spite of these elements of bias, the results of this trial may provide useful information for policy makers and developers of continuing medical education. The intervention is designed according to recently reported MRC guidelines and educational standards; exploratory analysis will reveal its successful elements. In the study design, bias is avoided if possible and still its setting is one of every day practice. Dissemination of the results of this study is planned for 2009.

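### The required size of 91 is stated in GPs, but whole practices or nurse groups are randomised, so the claimed power of 0.80 holds at the planning ICC only if clusters average about one GP

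*Protocol article*

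**What the plan says.** The section on sample size calculations in the protocol article plans for a change "from 50% to 65% of the total population of dementia". On allocation, "the ratio between the number of duos in the control group and the number of duos in the intervention group was 1:2". On clustering it states "Clusters are expected to include 5 patients on average" and "Intra class correlation (ICC) is expected to be 0.05 or lower". The result is given in GPs: "For a power of 0.80, and two-sided testing at 0.05, a total of 91 general practitioners is required".

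The section on bias control and randomisation defines the randomised unit: "A cluster was defined as all GPs working in the same practice or as all GPs working together with the same nurse". One of the factors balanced in the allocation is "cluster size (one vs. more than one GP"). The Discussion repeats the rule: "GPs from the same practices and GPs working with the same nurses are allocated to the same group".

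The study population section plans to recruit 100 duos, each made up of a GP and a nurse.

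**The concern.** The sample size paragraph and the randomisation paragraph use different units. The calculation ends in GPs, whereas the allocation is by practice or nurse group. A balancing factor that separates single-GP from multi-GP clusters shows that the authors expected some of the latter.

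A design effect of 1.20 belongs to independent clusters of 5 patients. If those 5 are the patients of one GP, a practice that contributes two GPs is a cluster of 10 and the design effect is larger. If those 5 are the patients of the whole practice, two GPs supply only one cluster between them. In both cases 91 GPs carry less information than the calculation credits them with. At stake is how a null result would be read: as coming from a trial with power 0.80, when that figure belongs to a design that randomises GPs one by one.

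**Working it through.** **Inputs from the sample size section:** proportions 0.50 and 0.65; control to intervention 1:2; two-sided alpha 0.05; power 0.80; 5 patients per cluster; ICC 0.05 (the upper planning value). **Input from the study population section:** 100 duos planned. **Assumption:** k, the mean number of participating GPs per randomised cluster. The article does not give it, so a range is shown.

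**Step 1: reproduce 91.** The pooled two-proportion formula without continuity correction gives 126 controls and 252 intervention patients, 378 in all (377.9 before rounding). The design effect is 1 + (5 − 1) × 0.05 = 1.20. Then 377.9 × 1.20 = 453.5 patients, and 453.5 / 5 = 90.7, so 91 clusters. The unpooled formula gives 91.4. Because the article calls these 91 GPs, one GP equals one cluster. Power is then 0.801. The reserve is very small: 455 / 377.9 = 1.204 is the largest design effect that 91 GPs can carry, which corresponds to k of about 1.02.

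**Step 2: reading A, 5 patients per GP.** A cluster holds 5k patients and the design effect is DE = 1 + (5k − 1) × ICC. The effective number of patients is 455 / DE for 91 GPs and 500 / DE for 100 duos. GPs needed are 377.9 × DE / 5 (the rows use 378, rounded up). At ICC 0.05:

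| k | DE | Power, 91 GPs | Power, 100 duos | GPs needed for 0.80 |
|---|---|---|---|---|
| 1 | 1.20 | 0.80 | 0.84 | 91 |
| 1.25 | 1.26 | 0.78 | 0.82 | 96 |
| 1.5 | 1.325 | 0.76 | 0.80 | 101 |
| 2 | 1.45 | 0.72 | 0.76 | 110 |
| 3 | 1.70 | 0.66 | 0.70 | 129 |

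At ICC 0.02 the same formula gives, with 91 GPs, 0.82 (k = 1.5), 0.81 (k = 2) and 0.78 (k = 3). With 100 duos it gives 0.86, 0.84 and 0.81.

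The article speaks of an average cluster size, so sizes will vary. With an assumed coefficient of variation of 0.5, DE = 1 + ((1 + 0.25) × 5k − 1) × 0.05. At k = 2 this is 1.575, and power with 91 GPs falls from 0.72 to 0.69.

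**Step 3: reading B, 5 patients per randomised cluster.** The design effect of 1.20 is then right, and 91 is the number of clusters. But 91 GPs form only 91 / k clusters. At k = 1.5 that is 60.7 clusters and 303 patients, or 303 / 1.20 = 253 effective patients, with power about 0.63. At k = 2 it is 45.5 clusters and 227.5 patients, or 190 effective patients, with power about 0.51. Under this reading 100 duos supply 91 clusters only while k is at most 100 / 91 = 1.10.

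**The case against.** The strongest reply is that nothing here shows the trial to be underpowered. Several parts of it stand.

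- **k is unknown.** The balancing factor shows that multi-GP clusters are expected, not how common they are. GPs are approached individually by mail across a province, and only participating GPs count. At k = 1.25 under reading A the loss is about 2 points.
- **The ICC is a ceiling.** The article expects 0.05 or lower. Under reading A at ICC 0.02, 91 GPs keep 0.81 at k = 2.
- **The plan is 100 duos, not 91.** Under reading A at ICC 0.05 this holds about 0.80 up to roughly k = 1.5.
- **The unit of the 5 patients is ambiguous.** The text says clusters, not GPs, so the formula with 5k may not be the one to correct.
- **These are powers of the planning model.** It compares patient-level proportions, whereas the primary outcomes are numbers of assessments and diagnoses over nine months.

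A reader might therefore infer from the table that the trial's power is 0.72, or that it cannot reach 0.80. The documents do not support that, because k and the true ICC are not given.

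The reply does not remove the point itself. The figure of 91 was computed at ICC 0.05, so the stated claim has to hold there. The margin of 100 duos also has to absorb any dropout and unequal cluster sizes, and under reading B it is used up at k = 1.10. Nor is this a detail left to a fuller document: the article states a specific number and attaches it to the wrong unit.

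**Conclusion.** The concern holds in conditional form. The required size is given in GPs while the randomised unit is the practice or nurse group, and 91 GPs match power 0.80 at ICC 0.05 only if clusters average about one GP. The direction is the same under both readings of cluster; the size of the loss is not fixed by the document. Under reading A at ICC 0.05 it runs from about 2 points at 1.25 GPs per cluster to about 15 at 3. The planned 100 duos offset it up to about 1.5 GPs per cluster, and a lower ICC could remove much of it. Under reading B the shortfall is larger. All these figures rest on assumed values of k and, except where the coefficient of variation is named, on equal cluster sizes.

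**What to change.** State whether 5 patients is per GP or per randomised cluster, then restate the calculation on the randomised unit.

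- **If per GP:** use design effect 1 + (5k − 1) × ICC with the expected number k of participating GPs per cluster, inflated for variable cluster size as 1 + ((1 + CV²) × 5k − 1) × ICC.
- **If per randomised cluster:** keep 1.20 (with an allowance for variable size if wanted), relabel 91 as clusters, and give the number of GPs that this implies.
- **In either case:** report the required number of clusters as well as GPs, and the power for the planned 100 duos over a plausible ICC range, for example 0.02 to 0.05.

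This rewrites one paragraph. The downside is that the stated power may look less favourable. The correction itself needs no extra recruitment and no change to the randomisation.

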### Statistical analysis

In addition to a confirmatory analysis using the MANOVA-method, we will also perform an exploratory analysis. The aim of the exploratory analysis is to gain more insight into possible causal relations between the rate of success of the intervention components and the outcomes. Possible mediator variables are change in knowledge, attitudes and collaboration rate. We will design a path-model, specifying hypothesized relations between predictors, mediators, moderators, and effects, and we will test its goodness of fit with the data. In this way we hope to be able to specify the most plausible interdependence pattern between the variables used in the present study.

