**Methods:**

The DTP is a complex educational intervention that consists of two workshops, a coaching program, access to an internet forum, and a Computerized Clinical Decision Support System on dementia diagnostics. One hundred duos of GPs and nurses will be recruited, from which 2/3 will be allocated to the intervention group and 1/3 to the control group. The effects of implementation of the DTP will be studied in a cluster-randomised controlled trial. Primary outcomes will be the number of cognitive assessments and dementia diagnoses in a period of 9 months following workshop participation. Secondary outcomes are measured on GP and nurse level: adherence to national guidelines for dementia, attitude, confidence and knowledge regarding dementia diagnosis and management; on patient level: number of emergency calls, visits and consultations and patient satisfaction; and on caregiver level: informal caregiver burden and satisfaction. Data will be collected from GPs' electronic medical records, self-registration forms and questionnaires. Statistical analysis will be performed using the MANOVA-method. Also, exploratory analyses will be performed, in order to gain insight into barriers and facilitators for implementation and the possible causal relations between the rate of success of the intervention components and the outcomes.

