## Methods

### Study design and setting

This study is an outcome assessor-blinded randomised controlled trial. A cluster-randomised design will be used to compare duos of GPs and nurses (Figure 1).

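### The only confirmatory analysis named, MANOVA, does not match randomisation by practice or nurse group and does not answer the hypothesis for each of the two primary counts

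*Protocol article*

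**What the plan says.** The confirmatory method appears twice. The abstract states: "Statistical analysis will be performed using the MANOVA-method". The Statistical analysis section states: "In addition to a confirmatory analysis using the MANOVA-method, we will also perform an exploratory analysis". The rest of that section is about the exploratory path model. It does not mention the cluster, the unit of analysis, the baseline count or an effect measure.

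The design is described as follows:

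- Study design and setting: "A cluster-randomised design will be used to compare duos of GPs and nurses".
- Bias control and randomisation: "A cluster was defined as all GPs working in the same practice or as all GPs working together with the same nurse". One of the balancing factors there is "cluster size (one vs. more than one GP"), so clusters with several GPs are expected alongside single-GP clusters.
- Outcome measures and data collection: "Primary outcome measures are the numbers of cognitive assessments and dementia diagnoses over a period of nine months", measured at baseline (T0) and at nine months (T1).
- Sample size calculations: "Cluster randomisation was taken into account when we calculated the sample size needed". The target there is a change "from 50% to 65% of the total population of dementia", which is a proportion of patients and not a count per duo.

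**The concern.** MANOVA in its usual form treats each row as an independent observation. Duos in the same practice, or sharing a nurse, are allocated together and are likely to resemble each other. If duos are the rows and the cluster is left out, the standard error is too small and the nominal 5% test rejects too often under the null.

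There is also a question of what the test shows. The abstract expects the programme to raise both the number of cognitive assessments and the number of dementia diagnoses. An omnibus test across the two is non-directional and can reject because only one of them moved. The programme trains assessment directly, so a rise in assessments without a rise in diagnoses is a plausible result, and a significant omnibus test would not distinguish it from success on both.

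Finally, the sample size is built on a two-group comparison of proportions with an ICC, which is a different model from a MANOVA on two counts.

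**Working it through.** **Inputs from Sample size calculations.** 50% versus 65%; control to intervention 1:2; two-sided 0.05; power 0.80; 5 patients per cluster; ICC 0.05 (the upper value given); result 91 GPs.

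**Step 1: reproduce the plan's figure.** Pooled proportion = (0.50 + 2×0.65)/3 = 0.60.

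Control n = [1.960×√(0.60×0.40×1.5) + 0.842×√(0.25 + 0.2275/2)]² / 0.15² = 126. Total = 126 + 252 = 378 patients.

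Design effect = 1 + (5−1)×0.05 = 1.2. Then 378×1.2 = 453.6 patients, and 453.6/5 = 90.7, so 91 GPs. The figure reproduces. Dividing by 5 to reach a number of GPs treats each GP as one cluster. Correlation between GPs in one randomised practice or nurse group does not enter this calculation.

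**Step 2: type I error if duos are the rows.** One row per duo already absorbs the correlation among patients of one GP. What remains is the correlation ρ between duos in the same randomised cluster. With J GPs per cluster, DEFF = 1 + (J−1)ρ. For a two-outcome test with the same DEFF on both outcomes, the actual size is approximately exp(−5.991/(2×DEFF)). J and ρ are assumptions, as the article gives neither.

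| J | ρ = 0.05 | ρ = 0.10 | ρ = 0.20 |
|---|---|---|---|
| 1 | 5.0% | 5.0% | 5.0% |
| 1.5 | 5.4% | 5.8% | 6.6% |
| 2 | 5.8% | 6.6% | 8.2% |
| 3 | 6.6% | 8.2% | 11.8% |

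Where ρ might lie: if the ICC of 0.05 also held between patients of different duos in a cluster, with 5 patients per duo, duo totals would correlate at 5×0.05/(1 + 4×0.05) = 0.25/1.20 = 0.21. That gives 8.4% for 2 duos per cluster (7.5% for a single outcome) and 12.1% for 3 (10.0%). If the 5 patients are instead the whole randomised cluster, 2 duos have 2.5 patients each, ρ = 0.125/1.075 = 0.116 and DEFF = 1.116. The single-outcome size is then 6.4%, and by the same route 6.9% for 3 duos.

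**Step 3: simulation on counts (assumed means 5 and 2.5).** Two sets of runs bracket the formula.

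- With 100 duos, the correlation placed on the underlying log rates and most scenarios mixing single-duo and larger clusters, duo-level MANOVA rejected in 4.7-6.5% of runs. Poisson noise makes the correlation of the counts lower than the value set.
- With 90 duos, every cluster of the same size and a between-duo correlation of 0.1, 0.2 or 0.3, it rejected in 5.7, 8.2 and 9.8% of runs for 2 duos per cluster, and in 8.7, 11.6 and 15.2% for 3.
- With one row per randomised cluster, rejection was about 4-5%.

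**Step 4: small counts alone.** With one duo per cluster, rejection was 4.4% (means 5 and 2.5) and 4.8% (means 1.5 and 0.7). Non-normality by itself does not inflate the error at about 100 duos.

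**Step 5: cost of testing the two outcomes separately.** At 91 GPs the effective sample is 91×5/1.2 = 379 patients, split 126 and 253. The standard error is 0.0534 under the null and 0.0536 under the alternative. Holm's first step uses 0.025, so z = 2.241. Power = Φ[(0.15 − 2.241×0.0534)/0.0536] = Φ(0.57), or about 0.71, against 0.80 at the 0.05 level. Restoring 0.80 takes about 110 GPs; at the planned 100 duos it is about 0.76.

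**The case against.** The strongest reply is that this is a condensed article. It names a method in half a sentence and never says that clustering will be dropped. A reader might infer that MANOVA here ignores the cluster and that its p-value is therefore too small. The document does not support that as a fact. The statement that the design compares duos describes the trial and does not define the rows of the analysis. A MANOVA with one row per randomised cluster would be valid, and the inflation disappears if every cluster holds one duo. This objection stands, and the error rates above are conditional for that reason.

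A reader might also infer that treating small counts as normal makes the p-value too small. Step 4 shows otherwise: the cost is in efficiency and interpretation. Nor does the lack of an exposure term bias the arm comparison, because allocation is random and balanced on cluster size and percentage of elderly patients. An offset improves precision and makes the result easier to interpret.

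Third, it is tempting to say that the plan yields no effect estimate. That is true of the omnibus statistic only. Separate estimates for each outcome are not excluded and may be set out in a document not shown.

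What the reply does not remove is that a specific confirmatory method is fixed, in two places, and that its standard form does not suit a design expected to include clusters of several GPs.

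**Conclusion.** The point holds as a mismatch between the stated method and the stated design. MANOVA as named assumes independent rows, while the randomised unit may contain several duos. If duos are the rows, the nominal 5% test runs at about 5.4-6.6% for an average of 1.5 GPs per cluster, 6-8% for 2 and 7-12% for 3, assuming a between-duo correlation of 0.05 to 0.20. It runs at 5% if every cluster holds one duo. The lower part of this range is plausible, since single-GP clusters are expected.

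Independently of clustering, the omnibus test does not establish whether assessments, diagnoses or both increased, and the sample-size model is not the model to be fitted.

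**What to change.** Replace MANOVA as the confirmatory analysis. For each primary count, fit a negative-binomial or Poisson model with a random intercept, or cluster-robust variance, for the randomised practice or nurse cluster. Adjust for the T0 count, and use an offset of the log of practice size times percentage elderly. An analysis with one row per randomised cluster would serve equally well. State the unit of analysis in either case. Report a rate ratio with 95% CI for each outcome, under a multiplicity rule fixed in advance, such as Holm.

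No new data are needed: the T0 count, practice size and percentage elderly are already collected. The cost is somewhat wider intervals and, with Holm, first-step power of about 0.71 per outcome rather than 0.80 at 91 GPs. That figure rests on the plan's comparison of proportions, so it is only indicative for a count model. The plan should state this loss.
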